## Abstract

**Background:**

Currently, non- or minimally displaced distal radius fractures are treated by 3 to 5 weeks of cast immobilisation. Many patients with a distal radius fracture suffer from long-term functional restrictions, which might be related to stiffness due to cast immobilisation. Current literature indicates that 1 week of immobilisation might be safe; however, no level 1 evidence is available. This trial aims to compare 1 week of brace immobilisation with 3 weeks of cast immobilisation in patients with distal radius fractures that do not need reduction.

**Methods:**

The aim of this trial is to evaluate the non-inferiority of 1 week of brace immobilisation in patients with non- or minimally displaced distal radius fractures. A two-armed single blinded multicentre randomised clinical trial will be conducted in three hospitals. Adult patients, between 18 and 50 years old, independent for activities of daily living, with a non- or minimally displaced distal radius fracture can be included in this study. The intervention group is treated with 1 week of brace immobilisation, and the control group with 3 weeks of cast immobilisation. Primary outcome is the patient-reported outcome measured by the Patient-Related Wrist Evaluation score (PRWE) at 6 months. Secondary outcomes are patient-reported outcome measured by the Quick Disabilities of the Arm, Shoulder and Hand score at 6 weeks and 6 months, PRWE at 6 weeks, range of motion, patient-reported pain score measured by VAS score, radiological outcome (dorsal/volar tilt, radial height, ulnar variance, presence of intra-articular step off), complications and cost-effectiveness measured by the EuroQol 5 Dimension questionnaire, Medical Consumption Questionnaire and Productivity Cost Questionnaire.

**Discussion:**

This study will provide evidence on the optimal period of immobilisation in non-operatively treated displaced and reduced distal radius fractures. Both treatment options are accepted treatment protocols and both treatment options have a low risk of complications. Follow-up will be according to the current treatment protocol. This study will provide level 1 evidence on the optimal period and way of immobilisation for non- or minimally displaced distal radius fractures in adult patients.

**Trial registration:**

ABR 81638 | NL81638.029.22 | www.toetsingonline.nl. 18th of October 2023

**Supplementary Information:**

The online version contains supplementary material available at 10.1186/s13063-024-08375-4.

## Background

The prevalence of distal radius fractures (DRFs) is bimodal; there is a peak at childhood age, concerning mostly male patients, followed by a peak in patients above 70 years of age, mostly woman [1]. Approximately 10–35% of all distal radius fractures (DRFs) are non- or minimally displaced (radial shortening < 3 mm, dorsal tilt < 10°, volar tilt < 20°) [2, 3]. Currently, the preferred treatment for non- or minimally displaced DRFs is immobilisation for 3 to 5 weeks in a cast or brace [4].

Literature shows that wrist joint stiffness is correlated with a longer period of immobilisation [5, 6]. Wrist stiffness may lead to a restricted range of motion and worse functional outcome. It is believed that stiffness is caused by restricted movement during cast immobilisation over a longer period of time [5]. The ideal treatment of DRF will be short, safe and will lead to an early return to work or daily activities, which is especially important in young and vital patients. In the past, non- or minimally displaced DRFs were immobilised for 4 to 6 weeks [7, 8]. Literature suggests that a shorter period of immobilisation is safe and might even accelerate and enhance functional outcome [9–12]. Recently, a systematic review on the duration of cast immobilisation concluded that a maximum of 3 weeks of cast immobilisation is equal in functional outcome and will not lead to more complications compared with a longer period of immobilisation in both displaced and non-displaced DRFs. Results of this study were limited by strength of available evidence as well as bias. Also, data were too heterogeneous to be pooled to perform a meta-analysis [13]. Beside functional benefits, it is plausible that shortening the period of immobilisation will aid independency and accelerated return to work or school. However, some fear complications such as secondary displacement and pain [9]. Secondary displacement is described as a complication of the non-operatively treated DRF, which occurs in 90% of the cases in the first 2 weeks following trauma, predominantly in displaced and closely reduced DRFs [14, 15]. Secondary displacement in non- and minimally displaced DRFs is very uncommon [3, 10, 16]. Furthermore, two studies stated that the only advantage of cast immobilisation within this group is the antalgic function, which might also support shorter treatment in vital patients [10, 17]. Bracing may provide a comfortable alternative to cast immobilisation. It will allow earlier movement and return to work and might lead to higher patient satisfaction and improvement of cost-effectiveness. Bracing is not related to increased risk of secondary displacement or other complications, as the fractures analysed in this study are non- or minimally displaced and therefore stable fractures. Many studies have been published on functional bracing in DRFs, none providing level 1 evidence [18–20].

This study was initiated to assess whether a period of 1 week of brace immobilisation within non- or minimally displaced DRFs is safe and will lead to an equal functional outcome, earlier return to work, higher patient satisfaction and reduction of health care costs compared to 3 weeks of cast immobilisation. The hypothesis of the study is that 1 week of brace immobilisation is non-inferior to 3 weeks of cast immobilisation.

This randomised controlled trial will provide level 1 evidence on the optimal period and way of immobilisation for non- or minimally displaced distal radius fractures in adult patients. Literature indicates that a shorter period of immobilisation and immobilisation by bracing is safe and might even be beneficial.

This study protocol is based on the ‘DR PIP II: Distal Radius Plaster Immobilization Period II’ study protocol (NL62861.029.17) where 4 weeks versus 6 weeks of cast immobilisation is analysed within displaced and reduced DRFs [21].

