Radiological outcome will be measured by the principal investigators of the participating hospitals; data will be cross checked by the clinical investigator; dorsal and volar tilt in degrees, radial height in millimetres and ulnar variance in millimetres will be calculated directly after trauma and after 6 weeks and 6 months. Complications contain secondary displacement (radial shortening > 3 mm, dorsal tilt > 10° or intra-articular step-off > 2 mm), delayed/non-union, re-interventions, complex regional pain syndrome (CRPS), tendon injuries (ruptures and tendinitis), nerve injuries (carpal tunnel syndrome and lesions) and distal radial ulnar joint disability.

Cost-effectiveness and cost-utility of non- or minimally displaced DRFs treated by 3 weeks of cast immobilisation or 1 week of brace immobilisation will be analysed. The perspective of this study is societal, and therefore both direct and indirect costs due to the DRF will be considered. Direct costs will include treatment, follow-up visits at the outpatient clinic, additional visits to health care professionals and the treatment of complications. Non-health care related costs include expenses to travel to and from the hospital. Indirect costs are based on absenteeism of work or loss of working hours due to cast-immobilisation or pain. To estimate health care costs, the friction-cost method will be used to analyse the loss of production for an individual worker. This analysis is based on a cost-effectiveness analysis of a study on the non-operative versus the operative treatment of DRFs [27]. To analyse cost-effectiveness and cost-utility, the EuroQol 5D (EQ-5D), Productivity Cost Questionnaire (iPCQ) and the Medical Consumption questionnaires (iMCQ) will be used [28–31]. Only the applicable items are included in this study. To create baseline data, patients will be asked to complete those questionnaires at the ED at the day of trauma (*t* = 0). Patients will also be asked to complete these questionnaires at 6 weeks and 6 months.

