### Statistical analysis

Data from the demographic data collection and the outcome parameters will be cleaned blindly from the treatment data. Data are presented as mean scores with 95% confidence intervals. Linear regression analysis will be performed if data are not normally distributed.

A blinded evaluation of the trial patient’s functional status will be performed by a research assistant by use of the PRWE and qDASH scores. Blinded radiographic evaluation will be performed the intervention group and the control group. An independent expert will assess the degree of dislocation on an X-ray, blinded from the first assessment. Final blinded analysis of the primary outcome parameters will only be performed after 6-month follow-up.

The analysis of this study will be carried out according to the intention-to-treat principle, i.e. the patients will remain in the group they will be randomly allocated to at the baseline. Analysis of functional outcome will be assessed using repeated-measures analysis of variance (GLM 4) with the time as the within-group factor and the treatment as the between-group factor. The post hoc analysis will be performed on the time of randomisation. Group comparisons at different time points will only be made when the overall repeated-measures tests are statistically significant. All scores will be tested for normality using the Kolmogorov–Smirnov test. Parametric variables will be compared using the Student’s *t*-test, while non-parametric and ordinal variables will be compared using the Mann–Whitney *U* statistic. Nominal variables will be compared across independent groups using the chi-squared test or Fisher’s exact test. Homogeneity of variance will be assessed using Levene’s test.

Baseline characteristics that will be analyses are gender, age, dominancy, fracture side, fracture characteristics, smoking and osteoporosis. The outcome will be tested for normality and according to the outcome mean or median baseline characteristics will be compared.

Primary and secondary outcome measures are functional outcome (PRWE and qDASH), return to work, range of motion, pain, radiological outcome, complications and cost-effectiveness.

Missing data of the PRWE and qDASH score during follow-up can be imputed using multiple imputation based on baseline characteristics

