The PRWE questionnaire will measure the primary outcome (PRWE after 6-month follow-up). In this questionnaire, pain and function are scored on a 0 to 10 scale. The total score can range between 0 and 100, with 0 being the best possible outcome and 100 the worst. The outcome will be tested for normality, and according to the outcome mean or median PRWE after 6 months will be calculated. The mean or median outcome after 6 months in the intervention group (e.g. 1 week of brace immobilisation) will be compared with the control group (e.g. 3 weeks of cast immobilisation). A *t*-test will be used to compare the different outcomes. A *p* value of < 0.05 will be taken as a threshold of statistical significance. To check for clinically relevant results, we will compare the outcomes between the two groups to check whether this difference will reach the minimal clinically important difference of the PRWE of 11.5. Different variables will be compared between the two treatment groups (e.g. 1 week of brace and 3 weeks of cast immobilisation groups). In addition, if possible, a multivariate analysis will be performed, to compare different secondary outcomes to the period of brace or cast immobilisation. Depending on the amount of missing data, we will impute outcomes using multiple imputation based on age, sex, smoking and fracture characteristics. For all analysis, SPSS statistical software (version 28.0) will be used, in which two-tailed *p* value < 0.05 will be considered significant.

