Therefore, it is important to provide level I evidence on bracing of DRFs. This study is designed as a randomised controlled trial with a non-inferiority design. Also, cost-effectiveness will be taken into account. The shorter the period of immobilisation, the earlier independency and return to work or school can be achieved, which will improve cost-effectiveness as well. Primary outcome of this study is the PRWE score after 6-month follow-up. The sample size of this study is based on the MCID of the PRWE. Functional self-reported outcome is considered as most important outcome factor. X-rays will also be analysed; however, secondary dislocation is not expected, as the non-displaced DRFs included in this study are considered to be stable. Furthermore, the correlation between radiological outcome and patient-reported outcome has been disputed in literature before. Functional outcome, especially patient-reported outcome, is the most important outcome factor. Radiological outcome does not always correlate to functional outcome, especially when aberrant outcome is subtle. But as very poor radiological outcome might influence other outcome factors, we chose to analyse this factor as well as a secondary outcome [39, 40].

This study will provide evidence on the optimal period of immobilisation in non-operatively treated displaced and reduced distal radius fractures. Both treatment options are accepted treatment protocols and both treatment options have a low risk of complications. Follow-up will be according to the current treatment protocol. This study will provide level 1 evidence on the optimal period and way of immobilisation for non- or minimally displaced distal radius fractures in adult patients.

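### The safety aim has no criterion, and the only comparison fixed for complications is a difference test whose non-significance could not by itself support a claim of safety

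*Protocol article*

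**What the plan says.** **Aim.** The Background of the Protocol article gives several reasons for starting the study. One is to "assess whether a period of 1 week of brace immobilisation within non- or minimally displaced DRFs is safe"; the others are equal function, earlier return to work, satisfaction and lower cost. It then gives the formal hypothesis: "The hypothesis of the study is that 1 week of brace immobilisation is non-inferior to 3 weeks of cast immobilisation". The Sample size calculation ties that hypothesis to the PRWE at 6 months, with a limit of 10.0 points. No margin or acceptable rate is given for complications.

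**Outcome.** Complications are one of the secondary outcomes in Methods/design: "Complications contain secondary displacement (radial shortening > 3 mm, dorsal tilt > 10° or intra-articular step-off > 2 mm), delayed/non-union, re-interventions, complex regional pain syndrome", followed by tendon injury, nerve injury and distal radio-ulnar joint disability.

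**Analysis.** Statistical analysis does not name complications when it assigns methods. The rule that covers them is general: "Nominal variables will be compared across independent groups using the chi-squared test or Fisher’s exact test". The threshold for all analyses is that a "two-tailed *p* value < 0.05 will be considered significant". That section mentions 95% confidence intervals only for mean scores.

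**Expected events.** The Background says "Secondary displacement in non- and minimally displaced DRFs is very uncommon". The Discussion says "secondary dislocation is not expected, as the non-displaced DRFs included in this study are considered to be stable" and describes complication risk as low with both treatments. No figure is given.

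**The concern.** A difference test asks whether the data contradict equal risk. A safety aim asks how large an excess risk remains plausible. When events are rare and the arms small, the test will usually be non-significant whether or not the brace raises the risk, so its result says little about that question.

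For function, the article deals with this by setting a non-inferiority limit. For complications it sets no counterpart, and the one comparison it fixes cannot take that role. A later report of no significant difference in complications could then carry more weight than it deserves. This matters because Methods/design would prefer the shorter treatment if it is non-inferior, reasoning from an ideal treatment that is short and safe, while the formal margin covers the PRWE only.

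**Working it through.** **Inputs from the Protocol article.** 34 evaluable patients per arm, 37 per arm recruited, PRWE limit 10.0, SD 14.0, power 90%, type I error 5%, two-tailed p < 0.05 for all analyses. Complication rates and any complication margin are assumptions, because the article gives none.

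**1. The plan's own sample size.** n = 2(z₀.₉₅ + z₀.₉₀)² × SD² / limit² = 2 × (1.645 + 1.282)² × 14² / 10² = 33.6, so 34 per arm. The stated figure is reproduced with a one-sided 5% level. It rests on the PRWE alone.

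**2. What Fisher's test needs.** With equal arms of size n and x events against 0, two-sided p = 2 × C(n, x) / C(2n, x).

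| Events | n = 34 | n = 37 |
|---|---|---|
| 5 v 0 | 2 × 278,256 / 10,424,128 = 0.053 | 2 × 435,897 / 16,108,764 = 0.054 |
| 6 v 0 | 0.025 | 0.025 |

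Five events in an arm is 5/37 = 13.5% or 5/34 = 14.7%.

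**3. The chi-squared alternative.** The article does not say when each test applies. Without continuity correction, χ² = 2n(ad − bc)² / (product of the four margins). For 4 v 0 and n = 37 this is 74 × 148² / (37 × 37 × 4 × 70) = 4.23, p = 0.040. For 3 v 0 it is 74 × 111² / (37 × 37 × 3 × 71) = 3.13, p = 0.077. The choice of test moves the threshold from 6 v 0 to 4 v 0, but at 4 v 0 the expected count is only 2 per arm, where the chi-squared approximation is poor. The 5 v 0 result in step 2 is therefore specific to Fisher's test.

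**4. What no brace events would show.** The exact two-sided 95% upper limit is 1 − 0.025^(1/n): 10.3% for n = 34 and 9.5% for n = 37.

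**5. What the difference interval would show (Newcombe, 95%).**
- 0 v 0: each Wilson upper limit is z² / (n + z²) = 3.84 / 40.84 = 9.4% for n = 37 and 3.84 / 37.84 = 10.2% for n = 34. The intervals are ±9.4 and ±10.2 points.
- 3 v 1, n = 37: the Wilson intervals are 2.8% to 21.3% and 0.5% to 13.8%, and the difference is 8.1 − 2.7 = 5.4 points. Lower limit: 5.4 − √(5.3² + 11.1²) = −6.9. Upper limit: 5.4 + √(13.2² + 2.2²) = +18.8.

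**6. Illustrative power of Fisher's test (exact enumeration, assumed rates).**

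| Cast v brace risk | n = 34 | n = 37 |
|---|---|---|
| 1% v 5% | 0.5% | 0.7% |
| 2% v 10% | 6.6% | 8.7% |
| 5% v 15% | 12.8% | 15.5% |
| 5% v 20% | 31% | 36% |

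The same enumeration with the uncorrected chi-squared test gives 27% and 30% for 2% v 10%, so a fivefold risk would still be missed in about 70% of trials.

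**7. Dependence on the acceptable excess.** With equal true rates p and margin m, one-sided 5% and 90% power, n = 2p(1 − p)(1.645 + 1.282)² / m². A 10-point margin at a 2% rate needs 34 per arm; a 5-point margin needs 68 at 1% and 135 at 2%. At such low counts this normal approximation is rough.

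**The case against.** The strongest reply is that the article nowhere says a non-significant complication test will be read as safety. That is correct. The chi-squared and Fisher rule is generic, names neither complications nor safety, and attaches no conclusion to a null result. A reader might infer that the protocol judges safety by that test or commits itself to misreading it; the text supports neither. What it does support is that the safety aim has no criterion and that the one comparison fixed for complications could not serve as one.

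Second, safety is one of several purposes in a Background sentence. The hypothesis is non-inferiority, sized on the PRWE, and the Discussion calls functional outcome the most important factor. This stands: safety is not shown to be the trial's leading question, and a rare secondary outcome need not drive the sample size.

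Third, displacement is not captured only as a yes/no event. Tilt, radial height and ulnar variance are also measured on continuous scales after trauma, at 6 weeks and at 6 months, radiographs are read blind, and pain is scored repeatedly. This stands too, and it means the safety question does not hang on one test. These measures do not cover re-intervention, CRPS, or tendon and nerve injury.

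Fourth, interval methods for secondary outcomes are often left to an analysis plan. Missing detail would be no finding. Here, however, the article does state an aim, a test and a threshold, and the test and threshold do not answer the aim.

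**Conclusion.** The point holds as a low-cost improvement. Safety is a stated aim without a criterion, and a non-significant chi-squared or Fisher result in about 74 patients could not by itself support it. The sizes that depend only on the sample size are these: Fisher's test needs 6 v 0 events to reach p < 0.05, and no brace events leaves an upper 95% limit of 9.5% to 10.3%. The power figures and the margin calculations are illustrations at assumed rates.

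Two stronger readings should be resisted. One is that the trial is too small and must be enlarged; the article does not claim to be sized for complications. The other is that 74 patients can never show safety. That depends on the excess one would accept: 34 per arm is about enough for a 10-point margin at a 2% rate when analysed by confidence interval, but not for 5 points even at 1%. An interval makes that dependence visible, and a p-value does not.

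**What to change.** **Statistical analysis.** For two outcomes, any complication (patients with at least one) and secondary displacement, specify:
- counts and risks per arm with exact 95% confidence intervals;
- the brace-minus-cast risk difference with a 95% confidence interval, naming one method in advance (Newcombe or Miettinen-Nurminen);
- any p-value only alongside the interval;
- a safety statement based on the largest excess risk the interval rules out, not on non-significance.

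Say also that the interval takes precedence, since the two can disagree: at 5 v 0 with 37 per arm, the Newcombe interval is +1.4 to +28.0 points while Fisher's p is 0.054.

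**Background.** Reword the safety aim as estimating complication risk in each arm, and the difference between arms, with confidence limits.

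**Cost.** A few lines of text and analysis, with no extra patients, visits or data. The downside is a more modest safety statement: with no events in either arm, the trial could say only that an excess above roughly 9 to 10 points is ruled out.

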## Methods/design

The aim of this trial is to evaluate the non-inferiority of 1 week of brace immobilisation in patients with non- or minimally displaced distal radius fractures. As the ideal treatment of DRF is short, safe and will lead to an early return to work or daily activities, non-inferiority of 1 week of brace immobilisation will be considered superior to a longer period of immobilisation. This hypothesis was also supported by the previous study performed by this study group [22].

Primary outcome is:

Patient-reported outcome measured by the PRWE score after 6 months

Secondary outcomes:

Patient-reported outcome measured by the Quick Disabilities of the Arm, Shoulder and Hand score (qDASH) after 6 weeks and 6 monthsPatient-reported outcome measured by the PRWE score after 6 weeksRange of motion after 6 weeks and 6 monthsPatient-reported pain score (VAS score) at arrival at ED, after cast/brace is applied, in the first week after brace/cast removal, at 6 weeks and 6 monthsRadiological outcome at 6 weeks and 6 monthsComplicationsCost-effectiveness measured by EQ-5D, iMCQ and iPCQ questionnaires

The PRWE is a validated 15-item (scored 1–10) self-reported questionnaire and is the best questionnaire for evaluating the patient-reported outcome in case of DRFs [23, 24]. Patients rate their outcome on a 0–10 scale on pain and functional outcome, and scores will be transformed to a 0–100 score. A higher score indicates greater disability. The DASH Outcome Measure is a validated 30-item self-reported questionnaire for patients with disorders of the arm, shoulder and hand [25, 26]. The QuickDASH (qDASH) is the shortened version of the DASH Outcome Measure, using 11 items instead of 30 (scored 1–5) to measure pain and functional outcome. At least 10 of the 11 items must be completed to calculate a score. The scores will be transformed to a 0–100. A higher score indicates greater disability.

Range of motion will be measured by using a goniometer: volar/dorsal flexion, radial/ulnar deviation and pronation/supination will be determined. Patient-reported pain score will be measured by using the VAS score. VAS score is a widely used method for pain assessments. Patients score their pain on a scale of 1–10. A higher score indicated a higher level of pain. The VAS score will be measured on the ED at arrival and after application of the brace of cast. Patients will also receive a dairy after cast removal to record their pain score.

Radiological outcome will be measured by the principal investigators of the participating hospitals; data will be cross checked by the clinical investigator; dorsal and volar tilt in degrees, radial height in millimetres and ulnar variance in millimetres will be calculated directly after trauma and after 6 weeks and 6 months. Complications contain secondary displacement (radial shortening > 3 mm, dorsal tilt > 10° or intra-articular step-off > 2 mm), delayed/non-union, re-interventions, complex regional pain syndrome (CRPS), tendon injuries (ruptures and tendinitis), nerve injuries (carpal tunnel syndrome and lesions) and distal radial ulnar joint disability.

Cost-effectiveness and cost-utility of non- or minimally displaced DRFs treated by 3 weeks of cast immobilisation or 1 week of brace immobilisation will be analysed. The perspective of this study is societal, and therefore both direct and indirect costs due to the DRF will be considered. Direct costs will include treatment, follow-up visits at the outpatient clinic, additional visits to health care professionals and the treatment of complications. Non-health care related costs include expenses to travel to and from the hospital. Indirect costs are based on absenteeism of work or loss of working hours due to cast-immobilisation or pain. To estimate health care costs, the friction-cost method will be used to analyse the loss of production for an individual worker. This analysis is based on a cost-effectiveness analysis of a study on the non-operative versus the operative treatment of DRFs [27]. To analyse cost-effectiveness and cost-utility, the EuroQol 5D (EQ-5D), Productivity Cost Questionnaire (iPCQ) and the Medical Consumption questionnaires (iMCQ) will be used [28–31]. Only the applicable items are included in this study. To create baseline data, patients will be asked to complete those questionnaires at the ED at the day of trauma (*t* = 0). Patients will also be asked to complete these questionnaires at 6 weeks and 6 months.

This study will be conducted as a single-blinded multicentre randomised clinical trial in three hospitals. In this study, 3 weeks of cast immobilisation is compared to 1 week of brace immobilisation. The inclusion procedure and the moment of randomisation are visualised in Figs. 1 and 2. Patients will be treated in a lower arm cast in a neutral position or in a prefabricated brace [32]. The follow-up after the immobilisation period will be the same for both groups and will be according to the current treatment protocol. Additional physiotherapy is advised and exercises to train wrist function will be given. The follow-up is 6 months. We used the SPIRIT checklist when writing our report [33].

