### Sample size calculation

The primary outcome will be the PRWE score at 6-month follow-up, of which the minimal clinically important difference is 11.5 points. To be conservative, we use a non-inferiority limit of 10.0. The SD of the PRWE is 14.0 [35]. With a power (1 − *β*) of 90% and a type I error (*α*) of 5%, a sample size of 34 patients per treatment group was calculated.

To allow a 10% drop-out, 74 patients will be included, 37 patients per treatment arm. We expect that all patients can be included within 1–1.5 year.

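### Methods/design would label a non-inferior 6-month PRWE result as superior, with no superiority test or benefit result required for that label

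*Protocol article*

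**What the plan says.** In the protocol article, Methods/design first gives the aim as non-inferiority and then adds a sentence on how that result will be read. The reason comes first: "As the ideal treatment of DRF is short, safe and will lead to an early return to work or daily activities". The reading follows: "non-inferiority of 1 week of brace immobilisation will be considered superior to a longer period of immobilisation". No condition is attached.

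Other parts of the article bear on this sentence:

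- **Hypothesis (Background):** "The hypothesis of the study is that 1 week of brace immobilisation is non-inferior to 3 weeks of cast immobilisation". No superiority hypothesis is stated anywhere.
- **Study questions (Background):** the trial was set up to assess whether the brace is safe and "will lead to an equal functional outcome, earlier return to work, higher patient satisfaction and reduction of health care costs".
- **Primary outcome (Methods/design):** "Patient-reported outcome measured by the PRWE score after 6 months". The scale runs "with 0 being the best possible outcome and 100 the worst" (Statistical analysis), so a positive brace-minus-cast difference means the brace is worse.
- **Margin (Sample size calculation):** "To be conservative, we use a non-inferiority limit of 10.0".
- **Discussion:** the benefit of shorter immobilisation is again stated as expected: "the earlier independency and return to work or school can be achieved, which will improve cost-effectiveness as well".

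**The concern.** A non-inferiority result on 6-month PRWE supports one statement: the brace is not worse than the cast by 10 points or more. It does not show that the brace is better on the PRWE or on anything else. The sentence in Methods/design turns the first statement into the second.

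The justification is also circular. Of the advantages it cites, only the shorter duration is true by design. Safety and early return to work are among the things the trial is meant to find out. A rule that takes them as given would attach the same label whether or not pain, 6-week function, complications, return to work or costs turned out to favour the brace.

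What is at stake is the main conclusion of a trial presented as level 1 evidence. The point is separate from how the margin is tested: a correctly run non-inferiority test would still be followed by a conclusion it cannot carry.

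**Working it through.** **Inputs.** From Sample size calculation: margin 10.0, SD 14.0, power 90%, type I error 5% (sidedness not stated), 34 per arm. From Statistical analysis: two-tailed p < 0.05. Assumed: a true difference of 0 for planning, which the article does not state but which reproduces its sample size.

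**Step 1: reproduce the plan's figure.** n per arm = 2 × [SD × (z for alpha + z for power) / margin]².

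- One-sided 5%: 2 × [14 × (1.645 + 1.282) / 10]² = 33.57, rounded up to 34. This matches.
- One-sided 2.5%: 2 × [14 × (1.960 + 1.282) / 10]² = 41.19, rounded up to 42. This does not match.

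The trial was therefore sized as a one-sided 5% non-inferiority design. Because the analysis section is two-tailed, both readings are carried below; the second corresponds to a 95% confidence interval.

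**Step 2: standard error.** SE = 14 × √(2/34) = 3.40, with 66 degrees of freedom.

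**Step 3: worst observed result that still earns the label.** Limit = margin − t quantile × SE.

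- One-sided 5%: 10 − 5.66 = 4.34 points worse.
- 95% confidence interval: 10 − 6.78 = 3.22 points worse.

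With all 37 per arm analysed, SE = 3.25 and the limits are 4.58 and 3.51.

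**Step 4: probability that the label is given.** From the non-central t distribution with 66 degrees of freedom and non-centrality (10 − d)/SE, where d is the true brace-minus-cast difference:

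| True difference d | One-sided 5% | 95% CI |
|---|---|---|
| 0 | 0.898 | 0.827 |
| 3 points worse | 0.654 | 0.529 |
| 5 points worse | 0.426 | 0.305 |

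For comparison, a two-sided 5% superiority test would favour the brace 2.5% of the time when d = 0.

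**Step 5: how often the labelled arm has the worse mean.** At d = 0 and one-sided 5%, by the normal approximation, non-inferiority is met with probability 0.903. Non-inferiority together with a worse observed brace mean has probability 0.903 − 0.5 = 0.403. The share is 0.403 / 0.903, about 45%.

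**Step 6: a limit on how far this goes.** For the brace to be significantly worse at two-sided 5%, its observed mean would have to be at least 6.78 points worse. That exceeds both limits in Step 3. At the planned SD and size, a brace shown to be significantly worse on the PRWE could not also receive the label.

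**The case against.** The strongest reply is that the sentence is a rationale and not a claim about PRWE scores. It opens with what an ideal treatment looks like, compares the brace with a longer period of immobilisation, and is called a hypothesis in the sentence that follows. This is the ordinary logic of a non-inferiority trial: if function is not worse, the shorter treatment is preferred. The hypothesis, sample size and design description are all non-inferiority, and Statistical analysis contains no step to superiority. On that reading, 90% at no true difference is simply the intended power. A brace that is truly 3 points worse lies inside the margin of 10 and the stated MCID of 11.5, so the plan itself would count it as non-inferior.

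Much of this stands, and it rules out three stronger readings:

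- **That the plan treats non-inferiority as proof of superiority.** The article says considered, not proven.
- **That no benefit is tested.** Methods/design lists 6-week PRWE and qDASH, range of motion, pain, complications and cost-effectiveness as secondary outcomes. Statistical analysis adds return to work and applies two-tailed tests. A result favouring the cast would still be analysed. The gap is only that the label does not depend on these results.
- **That the 90% or 83% is a false-positive rate.** It is one only if superior means a better PRWE.

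The objection does not rescue the wording. Superior has a settled meaning beside a non-inferiority hypothesis, the sentence stands in the methods without qualification, and someone following it as written would report superiority. If a preference was meant, the text should say so.

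**Conclusion.** The point holds as a fault in the stated conclusion, not in the design, data collection or primary test. Methods/design attaches the word superior to a result that shows only that the brace is not worse by 10 points or more. It justifies this by advantages the trial has yet to establish.

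On the plan's own figures, the label would cover an observed brace mean up to 4.3 points worse (one-sided 5%) or 3.2 points worse (95% confidence interval). With no true difference it would be given about 90% or 83% of the time. These figures rest on SD 14, 34 analysed per arm and a correctly run non-inferiority test against the margin of 10. They describe how readily the label is earned. Whether they also measure error depends on what superior was meant to convey, which the article does not settle. The sentence should be corrected before analysis because it governs the headline conclusion and is easy to change.

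**What to change.** Delete the sentence, or reword it so that:

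- non-inferiority on 6-month PRWE supports only the conclusion that the brace is not worse than the cast by 10 points or more;
- the shorter treatment may then be described as preferred on that basis, with the observed secondary results reported alongside;
- superior is used only for an outcome on which a pre-specified superiority test is met after non-inferiority has been shown. Examples are a 95% confidence interval for the PRWE difference lying wholly below 0, or a test on a named benefit endpoint already collected.

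Which endpoints to use, and in what order, is for the sponsor to decide. No particular sequence is needed to repair the sentence.

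The cost is a change of wording and, if a superiority claim is wanted, one or more ordered tests on data already planned. No extra patients or visits are needed. The downside is a less favourable headline if no benefit is shown. Superiority on the 6-month PRWE itself would be hard to reach: with SD 14 and 34 per arm, a true 5-point advantage would meet a two-sided 5% test only about 31% of the time (normal approximation).
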